
## Methods

This protocol was developed in accordance with the SPIRIT (Standard Protocol Items: Recommendations for Interventional Trials) statement (Checklist 1) [23].

### Design and Setting

The study will be conducted in 2 phases: the development of the intervention using co-design principles (phase 1) and the pre-post interventional study (RECARD trial; phase 2).

#### Phase 1: Trial Development

Phase 1 will be conducted in 2 parts, A and B.

##### Phase 1 Part A: Evidence and Stakeholder Informed Approach Underpinned by Implementation Science

To design the study procedure and intervention bundle, a scoping review has been completed to identify effective, evidence-based elements of a pharmacist-led TOC service [1]. This review found that pharmacist-led TOC services incorporating diverse inpatient and postdischarge activities improve medication safety and care coordination for patients with cardiovascular disease. Moreover, tailoring TOC services to specific patient populations and targeting care toward high-risk patients were important aspects to consider for pharmacist-led TOC services to support improved patient outcomes.

The findings from the scoping review were combined with feedback from key stakeholders (clinicians and consumers) to understand their needs when transitioning from the hospital. This approach ensured an evidence-based and contemporary approach to delivering an effective service to prevent readmission [1]. The objective of the stakeholder engagement was to understand current practice (positive and negative elements) and ascertain perspectives from hospital-based and primary care providers pertaining to the coordination of health care both during and after hospitalization. Local requirements for the TOC service were also gauged, with a focus on optimal medication management and exploring patient needs to incorporate within the new model. To ensure a culturally informed intervention, our research team has worked closely with the Institute for Urban Indigenous Health, a community-controlled health organization servicing clinics across the Greater Brisbane region, and formed a reference group comprised of Indigenous community members and Institute for Urban Indigenous Health staff.

The data gathering, mapping, and reference group formation have used a combination of focus groups, semistructured interviews, and yarning, as well as service and patient journey mapping. Applying Bradshaw’s approach, the study assessed the 4 “needs“ below [24]:

Expert need: The gap between current practice provided at the hospitals when compared to the evidence for effectiveness when tailoring a TOC service to ensure that it is culturally appropriate and accessible. This has been identified in the scoping review and stakeholder focus groups [1].Expressed need: The way patients engage with the services or hospitals in their community.The felt needs of health care providers: The experiences and expectations of hospital health care providers, community pharmacists, and GPs (family doctors) to caring and discharging of this patient group.The felt needs of high-risk patients with cardiovascular disease: These are the care and knowledge gaps identified, and the experiences, expectations, and preferences reported by patients with cardiovascular disease about their hospital and postdischarge experiences.

Further details of phase 1 of this study are published elsewhere [25]. The bundle of care arising from the stakeholder involvement stages has informed the individualized care provided within the TOC service.

##### Phase 1 Part B: Risk Prediction Modeling

Risk prediction models to identify the risk of hospital readmission have been increasingly used in research to optimize care delivery and derive clinical benefit. In the AMI-CS cohort, models have been developed to predict 90-day readmissions with reasonable predictive performance [26,27]. However, these models omit medication-specific variables, and given the poor outcomes associated with early readmission, there is a need to develop a model to identify 30-day medication-related readmissions.

###### Aim

To develop and validate a risk prediction model to identify patients at risk of unplanned medication-related 30-day readmissions after an AMI and/or CS.

###### Methods

The model will be developed and validated using pretrial data from 1 to 2 Queensland hospitals. One thousand patients with a primary diagnosis of AMI and/or CS admitted to the PAH or TUH from July 2023 to June 2024 will be included in the model development study. Learnings from the development of a prior risk prediction model for medication harm [28] will be used to inform the new risk model.

Data will be collected from digital systems on patient characteristics, comorbidities, length of hospital stay, clinical parameters, and reason for admission. Other clinically relevant criteria not currently known will be identified through our consolidation of the literature [1] and data from part A.

###### Outcome

Medication-related hospital readmissions within 30 days of hospital discharge will be identified through a comprehensive retrospective review of patient clinical records by 2 senior pharmacists. Causality, preventability, and severity of potential medication-related hospital readmissions will be reviewed and rated by a panel of clinicians, including a cardiologist, nurse practitioner (NP), and pharmacist.

###### Statistical Analysis

Model evaluation will be guided by best practice guidelines, such as TRIPOD (Transparent Reporting of a Multivariable Prediction Model for Individual Prognosis or Diagnosis) statement [29], and the framework proposed by Steyerberg and Vergouwe [30] for developing robust prediction models.

Assuming an estimated medication harm readmission rate of 7% and the inclusion of 4 to 8 variables in the final model, a minimum events per variable ratio of 5 to 10 would suggest that at least 570 patients will be required, of whom approximately 40 will have medication harm readmission events.

Each variable will be evaluated using standard descriptive statistics and assessed visually to determine if it meets the basic assumptions for regression analysis. Missing data for each variable will be calculated, and where necessary, imputation methods will be used to conduct the analysis. Variables with more than 20% missing data will be excluded from the analysis. Univariable binomial logistic regression will be used to further assess the viability of candidate variables for multivariable analysis. Following this, we will fit a multivariable logistic regression model using an optimal subset of the candidate variables selected through either a penalized regression technique, such as LASSO (Least Absolute Shrinkage and Selection Operator) or elastic net [31,32], or by direct selection based on clinical relevance.

Predictive performance will be measured using the area under the receiver operating characteristic curve, as well as the area under the precision-recall curve. Sensitivity, specificity, positive predictive value, and negative predictive value will also be assessed at a cutoff chosen to classify the proportion of patients who will receive the intervention as “high-risk.” These metrics will be tested through cross-validation and reported for the best-performing model(s). Brier scores and calibration plots will be used to evaluate model calibration.

A deployable version of the optimally predictive model will be developed for use by clinical staff during phase 2 of the study. Patient data will be input by clinical staff, who will then be shown a prediction of the patient’s risk of medication-related readmission. The performance of the model will also be assessed at the end of phase 2.

### Phase 2: Pre-Post Interventional Study (RECARD Trial)

This study will use a pre-post study that compares a retrospective historical cohort that received usual care and without a TOC service (precohort) to a prospective cohort that includes patients who receive either usual care or a pharmacist-led interdisciplinary TOC service (postcohort; Figures 1 and 2). During the poststudy period, patients identified as high risk will receive the individualized TOC service. These patients will be determined as those at the highest risk of medication-related hospital readmissions and will be termed “high-risk patients.” The rationale for delivering the TOC service intervention to high-risk patients is to ensure that those at greatest need (ie, risk of medication harm and readmission) are prioritized and thereby supporting long-term service sustainability.

The current local funding models do not allow every patient to receive an individualized service. We need to ensure a sustainable model of care that has the potential to be implemented and maintained within the Australian health care setting.

**Figure 1. F1:**
[figure not shown]
The trial schema outlining the RECARD (Reduce Hospital Readmissions for High-Risk Cardiology Patients) pre-post trial. RE-AIM: Reach, Effectiveness, Adoption, Implementation, and Maintenance; TOC: transition of care.

**Figure 2. F2:**
[figure not shown]
Pre-post study diagram showing the 2 study periods and outlining participants who will receive the study intervention vs usual care. RECARD: Reduce Hospital Readmissions for High-Risk Cardiology Patients.

### Precohort

All patients admitted to the study sites with an index admission for AMI or CS between July 1, 2023, and June 30, 2024, will be included. A waiver of consent has been granted to collect these retrospective data for the historical usual care control group.

### Postcohort

All patients admitted to the study sites with an index admission for AMI or requiring CS between December 2025 and November 30, 2026; the period when the interdisciplinary pharmacist-led TOC service will be implemented.

### Eligibility Criteria

The inclusion criteria are as follows:

Aged ≥18 yearsDischarged from PAH, RBWH, or TUH for an index diagnosis of AMI, or discharged from PAH or TUH for a CS admissionWilling and able to provide informed consent

The exclusion criteria are as follows:

Patients who are palliative or receiving end-of-life carePatients undergoing chemotherapy, radiation therapy, or dialysisPatients transferred to nonstudy hospitalsPatients who discharged against medical advicePatients who died during their admissionPatients admitted with type 2 myocardial infarctionPatients who reside outside of QueenslandPrevious RECARD patients returning with a new AMI or CS event

The intervention period will require prospective collection of data for patients in the intervention group, who will be consented before receiving the TOC service. Patients who receive usual care have a waiver of consent to collect inpatient data and readmission data (Figure 2).

### Participant Identification, Recruitment, and Consent

Patients in the prestudy cohort will be retrospectively identified using the Health Information Management System reporting information and *International Statistical Classification of Diseases and Related Health Problems, Tenth Revision* (*ICD-10*; or equivalent) data. In contrast, patients in the postcohort will be identified through the presenting diagnosis (AMI or CS) or through a confirmed diagnosis on completed angiograms as per clinical records.

In the poststudy cohort, only patients identified as high-risk of readmission, either by the risk prediction model or by referral from the treating team, will be offered the TOC service model. Patients who are not identified as high-risk will receive usual care.

Patient recruitment will be completed by the TOC pharmacist or a member of the research team after patient identification by a member of either the TOC team, the research team, or the local treating team.

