### Statistical Analysis

An intention-to-treat analysis will be conducted. Participants who are lost to follow-up (ie, participants who do not complete the intervention, withdraw consent, or die during the study) will be included in the intention-to-treat analysis for the primary outcome. Participant characteristics will be summarized according to the prestudy and poststudy cohorts. Characteristics will be summarized and presented descriptively using mean (SD), median (IQR), and n (%), as required. Independent *t* tests and chi-square tests will be undertaken to determine whether there are any differences in baseline characteristics between the prestudy and intervention cohorts.

The primary outcome is a comparison of 30-day medication-related hospital readmissions in the prestudy cohort compared with the poststudy cohort. Secondary outcomes will be compared similarly. The analysis will consist of multivariable logistic regression. The explanatory variables will consist of a variable indicating the study period along with any relevant potential confounding variables we wish to control for (eg, patient age, sex, etc). The results for these outcomes will be considered significant at the 5% level, with 95% CIs reported. Subgroup analysis will also be undertaken to assess whether the clinical impact of the intervention varied by location (regional vs metropolitan sites), Indigenous and non-Indigenous patients, and high-risk patients identified according to the model of treating team referral.

Evaluation will be conducted using the RE-AIM framework as described earlier [20]. Data will be analyzed descriptively, and other metrics (eg, primary outcome) will be mapped as calculated above or informed by the patient survey and economic analysis.

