### Limitations

A key limitation of this pre-post study design is the potential failure to achieve the intended recruitment target in the postintervention phase, for which there are no clear mitigation strategies. This may reduce statistical power and limit the ability to detect meaningful differences between periods. However, to date, the study is progressing well with recruitment. Additionally, the retrospective-prospective nature of the design involves comparing different patient cohorts across separate time periods, meaning that the groups are not strictly comparable. Temporal changes in patient characteristics and clinical practice may confound the results, making it difficult to attribute observed differences solely to the intervention. This risk can be managed as some confounders can be accounted for or adjusted for in our statistical analysis. A controlled cohort design could have improved comparability and reduced bias; however, such an approach was not feasible in this context. Specifically, withholding a gold-standard medication management service from high-risk patients—who are most likely to benefit—would raise ethical concerns, necessitating the use of a less rigorous but more ethically appropriate pre-post design.

The study is among the first to determine whether a pharmacist-led Cardiology TOC service reduces 30-day medication-related patient readmissions and secondary outcomes. The findings will inform future implementation of a sustainable cardiac TOC model within the Australian health care setting.

The recent publication of the Medication Management at Transitions of Care Stewardship Framework by the Australian Commission [48] emphasizes that TOC, especially from the hospital to the home, is a high-risk period for medication errors, miscommunication, and preventable harm and therefore requires a structured stewardship approach to improve safety and outcomes. It outlines 4 core elements: strong governance through a designated committee, a multidisciplinary stewardship team to lead and champion improvements, coordinated medication management activities from admission to postdischarge, and continuous monitoring, evaluation, and feedback. The framework highlights person-centered care, effective communication, and digitally enabled information sharing as essential enablers, stressing early risk assessment, clear roles between providers, medication reconciliation at every transition, and robust, timely discharge communication [48].

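### The two cohorts share eligibility criteria but are found by different case-finding rules, so the study-period term in the primary analysis also carries any difference in ascertainment

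*Protocol article*

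**What the plan says.** Protocol article, Participant Identification, Recruitment, and Consent, gives one rule per period. For the first: "Patients in the prestudy cohort will be retrospectively identified using the Health Information Management System reporting information" together with ICD-10 or equivalent data. For the second: "In contrast, patients in the postcohort will be identified through the presenting diagnosis (AMI or CS) or through a confirmed diagnosis on completed angiograms", taken from clinical records. The second sentence covers the whole postcohort, usual-care patients included; the section narrows to high-risk patients only in its next paragraph.

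The Precohort and Postcohort sections aim at the same population, all index AMI or CS admissions at the study sites in a 12-month window. Eligibility Criteria gives a single list, tied to the diagnosis or procedure for which the patient was discharged.

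Statistical Analysis states: "The primary outcome is a comparison of 30-day medication-related hospital readmissions in the prestudy cohort compared with the poststudy cohort". On the model it says: "The explanatory variables will consist of a variable indicating the study period along with any relevant potential confounding variables we wish to control for", with age and sex as examples.

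Limitations concedes that "the retrospective-prospective nature of the design involves comparing different patient cohorts across separate time periods, meaning that the groups are not strictly comparable". It attributes this to calendar time, patient characteristics and clinical practice, and does not mention case finding.

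**The concern.** A discharge code is assigned after the stay, when the diagnosis is settled. A presenting diagnosis is a working diagnosis at the start. The two can pick out different patients under the same eligibility criteria, chiefly AMI patients whose infarction was recognised late or arose during another admission and who had no angiogram. Such patients can be in the precohort and absent from the postcohort.

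Case-finding method and study period coincide exactly, so the model has no information with which to separate them. The period coefficient is the sum of the intervention effect, the calendar-time change that the authors acknowledge, and the ascertainment difference that they do not. Adjustment for age, sex or comorbidity works on patients in the data set; it cannot restore those who never entered it. Calendar time is inherent in a pre-post design. The difference in case finding can be removed.

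**Working it through.** **1. Is there a passage that aligns the two routes?**

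| Section | Precohort | Postcohort |
|---|---|---|
| Precohort / Postcohort | all index AMI or CS admissions, July 2023 to June 2024 | all index AMI or CS admissions, December 2025 to November 2026 |
| Eligibility Criteria | one shared list | one shared list |
| Participant Identification | information system and ICD-10 data | presenting diagnosis, or diagnosis confirmed on angiogram |
| Data Collection | same variables | same variables |

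The last row aligns the data items, not how patients enter. Nothing states that the postcohort will be rebuilt from, or checked against, coded data, or that the precohort will be checked against presenting diagnosis or angiogram records.

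**2. The plan's own figures.** Inputs from Sample Size: 7% against 4.9%, significance level .05, power 0.80. The two-sided pooled-variance formula without continuity correction is

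n = [1.960·√(2·0.0595·0.9405) + 0.842·√(0.07·0.93 + 0.049·0.951)]² / 0.021² = 1990.8,

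against 1990 stated (power at 1990: 79.99%). Then 1990/0.90 = 2211.1, against 2211 stated. These reproduce, and the concern leaves them untouched. They show the scale: the target is 2.1 points.

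**3. Illustration, on assumed inputs.** Let a fraction f of the patients whom coding would find be missed in the post period, with risk m times the 7% average, and let there be no true effect. Then

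post rate = (0.07 − f·m·0.07)/(1 − f), and the spurious fall = 0.07·f·(m − 1)/(1 − f).

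The last column is the two-sided rejection rate at 1990 per period (unadjusted test of two proportions, nominal 5%).

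| f | m | Post rate | Spurious fall (points) | Share of 2.1 | Rejection rate |
|---|---|---|---|---|---|
| 5% | 1.5 | 6.82% | 0.18 | 9% | 5.6% |
| 5% | 2 | 6.63% | 0.37 | 18% | 7.5% |
| 10% | 1.5 | 6.61% | 0.39 | 19% | 7.8% |
| 10% | 2 | 6.22% | 0.78 | 37% | 16.7% |
| 5% | 0.5 | 7.18% | −0.18 | −9% | 5.6% |
| 10% | 0.5 | 7.39% | −0.39 | −19% | 7.6% |

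Worked example: f = 0.10, m = 2 gives (0.07 − 0.014)/0.90 = 0.0622, a fall of 0.78 points.

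The document gives neither f nor m. With m above 1 the bias favours the service; with m below 1 it hides a benefit.

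**The case against.** The strongest reply is that the identification section says how candidates are found, while the shared eligibility list says who belongs. Much of that stands:

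- A patient who presents as AMI but leaves with another diagnosis fails the discharge criterion, so most of the flow in that direction is removed.
- The post rule is presenting diagnosis **or** angiogram, so a conservatively managed patient who presents with AMI is still captured. Some of the patients who remain unfound may be type 2 infarctions, excluded in both periods.
- For CS the operation itself largely defines the case, so the problem is mainly one of AMI. A loss of 5-10% of the combined cohort has no basis in the document.
- Real-time recruitment cannot wait for discharge codes, and a condensed article may omit reconciliation of screening logs with coded data.

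This narrows the concern but does not remove it. Eligibility criteria can exclude a patient who was found; they cannot admit one who was not. The article also states the contrast between the two rules outright, so this is more than an omitted detail.

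A reader might also infer that the exclusion of previous RECARD patients bars precohort members with a new event from the postcohort, with no matching look-back for the precohort. The document does not settle this. The Introduction uses the term for patients of the TOC service, in which case the exclusion merely prevents re-enrolment; Informed Consent treats both periods as cohorts of the RECARD trial. The wording needs clarifying, but no bias can be computed from it.

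**Conclusion.** The concern holds in a limited form. The plan as written uses a different case-finding rule in each period, compares the whole cohorts on a period term, and describes no step that puts them on a common basis. Any difference in ascertainment goes straight into the primary estimate.

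It would be tempting to say that the two cohorts are different populations, or that the bias favours the intervention by 0.18-0.78 points. The document supports neither. Target population and eligibility criteria are shared, and the figures are one scenario that assumes 5-10% missed at 1.5-2 times the average risk; at half the average risk the shift is −0.18 to −0.39 points. What can be said is that the sign and size are unknown and that the target difference, 2.1 points, is small enough for a modest loss of patients to matter.

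**What to change.** **Change.** For the primary and all other pre-post outcome analyses:

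1. Define both cohorts from the same hospital information system and ICD-10 extract, with one code list, one set of exclusions and one index-admission rule. Run it for the post period once coding has closed. Keep presenting diagnosis and angiogram only as the real-time screen for offering the service.
2. Report the overlap between the screened and coded lists for the post period.
3. Add a sensitivity analysis that retains every consented, treated patient without a qualifying code. This addresses the tension with the intention-to-treat commitment in Statistical Analysis.
4. State the repeat-patient exclusion so that it works identically in both periods (first index admission within each 12-month window), and account for anyone who appears in both, for example with cluster-robust standard errors.

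**Cost.** One further run of an extract of the kind already used for the precohort, a wait for coding to close, and a few treated patients counted only in the sensitivity analysis. Recruitment, the intervention and the sample size do not change. Usual-care post patients are already under a consent waiver for inpatient and readmission data, and ICD-10-AM codes are already used for outcomes. Analysis is planned for January to March 2027 with no preliminary analysis undertaken, so the rule can still be fixed before results are seen.
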